## 1. Introduction

Hypoxic–ischemic brain injury during the birth process is manifested as neonatal encephalopathy after birth, termed hypoxic–ischemic encephalopathy (HIE) [1]. Estimated to occur in 1–7/1000 live births [2], it is a significant cause of neonatal death and cerebral palsy, epilepsy, hearing loss, and visual impairment [3,4]. Induced therapeutic hypothermia initiated within six hours of birth substantially reduces risk of death and moderate–severe neurodevelopmental disability at 18 months, with a number needed to treat of 7 [5]. Unlike motor impairment, hypothermia does not reduce the risk of neurocognitive deficits that may not be evident until school age [6]. Even in the absence of cerebral palsy, neonates with HIE exposed to hypothermia therapy are at risk of having an IQ score of <70 (11%) or 71–84 (32%) at school age [7]. Although not as debilitating as cerebral palsy, abnormalities of cognitive functions, such as attention deficits, learning disabilities, and abnormalities of visuospatial processing and executive functioning, will have profound and long-lasting negative impacts on a child’s language skills, academic performance, and quality of life. Being able to anticipate the risk of neurologic deficits in early infancy, the crucial formative period of brain development, may facilitate early interventions and improve outcomes. Early developmental intervention programs may include targeted speech–language therapy, physical therapy, parental coaching, parent–infant relationship enhancement, infant stimulation, psychological therapy, sensory modulation, and biofeedback therapy [8,9,10,11].

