#### 2.7.2. Experimental Setup

We made the customized neonatal cap stitched in 3 sizes to snugly fit head circumferences of 33 cm, 35 cm, and 38 cm (Figure 3). The cap could be slightly stretched in all directions, allowing us to accommodate multiple head sizes and shapes without affecting the channels’ positions that correspond to the anatomical landmarks of the brain. We determined the optode positions based on the 10–20 international EEG system [35] for electrode placement. Each transmitter–receiver pair had a 2 cm distance between them as specified by the device (Figure 4). The cap had 20 emitters and 16 detectors, with 27 channels per side covering the frontal, parietal, and occipital lobes (Figure 4).

We will first set up the cap by placing the transmitter and receiver optodes into the optode holders based on the cap layout. We will start recording to take measurements during natural sleep. All infants will be breathing spontaneously in room air. No sedation will be given to the infant. Parents will be encouraged to be at the bedside, and the infant will be cuddled in a warm blanket before being placed in the cot. All recordings will be taken within two hours after feeding in a dimly lit room in the NICU. The total duration of the resting-state data acquisition will range from 30 to 45 min, depending on the infant’s cooperativeness.

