### 2.8. Objectives and Outcomes

#### Objectives and Corresponding Outcomes of the Feasibility Trial

Objective 1: To determine the feasibility of recruitment and retention strategies and data collection methods in the NICU. Feasibility will be assessed by reporting the following metrics: (i) The recruitment rate will be reported to assess the ability to recruit the target population within the desired timeframe, determined by the number of eligible participants who are enrolled in the study. We will maintain a recruitment tracking log. (ii) The follow-up rate will be used to assess the ability to retain participants and complete follow-up assessments, as determined by the percentage of enrolled patients who complete follow-up at 12 months. We will maintain a record of participant follow-up procedures and dropout rates. (iii) The rate of missing data will be determined by the percentage of completed data fields measured by reviewing collected data to identify any missing information, inconsistencies, or incomplete responses. *Criteria for Feasibility:* The main study will be feasible if the pilot study is successful based on the predefined criteria: (i) 80% of the eligible patients consent to the testing; (ii) 90% of the consented participants get DOT measurements taken before 7 days of life; (iii) for 80% of the consented participants, parent-reported developmental assessment is available at 6 and 12 months.

Objective 2: To assess the fidelity and safety of DOT measurements in neonates. (i) Safety will be assessed by reporting any adverse skin reactions to sensors or excessive agitation in the neonate, requiring early termination of the study. (ii) Data quality will be assessed by recording the degree of the signal-to-noise ratio. We will keep a record of the ability to properly place sensors with good contact and the ability to minimize motion artifacts and ambient light interference in each subject. (iii) Ability to complete adequate data acquisition within 45 min. *Criteria for Feasibility:* Time required for resting-state data acquisition per infant < 45 min.

Objective 3: To identify logistic challenges, unexpected adverse effects, or technical difficulties. Operational feasibility will be assessed based on the time and personnel required for each stage of the study, as well as the logistical challenges.

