### 2.10. Sample Size and Recruitment

The National Center for Complementary and Integrative Health notes that sample size should be based on practical considerations, including participant flow, budgetary constraints, and the number of participants needed to reasonably evaluate feasibility goals [47]. Hence, for this work, a sample size of 25 was considered adequate to reach saturation and establish feasibility. If the feasibility criteria are met, the sample size for the larger trial will be determined based on the data analysis.

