**Secondary Aims**			
**Objectives**	**Outcome**	**Hypothesis**	**Analysis**
To explore the differences in brain metrics between male–female, mild–moderate–severe encephalopathy groups.	Brain metrics.	Significant difference in regional brain metrics.	Student *t*-test.
To explore the correlation of severity of brain injury score with brain metrics.	MRI injury score.	We can determine the required sample size for a definitive trial.	Regression analysis.
Correlation of brain metrics with neurological outcome.	ASQ scores at 6 months and 12 months.	We can determine the required sample size for a definitive trial.	Regression analysis.

**Table 2 neurosci-06-00060-t002:** Participant timeline.

	Study Period								
	Enrollment	Allocation	Post-Allocation						Close Out
Timepoint		Day 0	1–3 days	4–7 days	4–15 days	NICU discharge	6 months	12 months	
Screening for eligibility	X								
Approaching parents for informed consent	X								
Study ID created	X								
Allocation	X								
Clinical data collection	X	X	X	X	X	X			
Therapeutic hypothermia			X						
EEG monitoring			X						
MRI brain				X					
DOT measurement					X				
ASQ-3							X	X	
ASQ: SE-2							X	X	

Abbreviations: ASQ-3, Ages and Stages Questionnaire-3rd version; ASQ: SE-2 Ages and Stages Questionnaire: Socio-emotional-2nd version; MRI, magnetic resonance imaging; DOT, diffuse optical tomography; EEG, electroencephalogram.

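### The 12-month retention criterion is a percentage of all consented infants, so a death after consent counts as a failure to retain

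*Protocol article*

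**What the plan says.** Section 2.8, Objective 1, sets predefined criteria on which the feasibility of the main study depends, and Table 1 repeats them. Two use all consented infants as the denominator. Criterion (ii) is that "90% of the consented participants get DOT measurements taken before 7 days of life". Criterion (iii) is that "for 80% of the consented participants, parent-reported developmental assessment is available at 6 and 12 months". The same section presents the follow-up rate as a measure of the ability to retain participants, "as determined by the percentage of enrolled patients who complete follow-up at 12 months". The text shown does not separate deaths from withdrawal or loss to follow-up in any of these figures.

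The Introduction says of HIE that "it is a significant cause of neonatal death and cerebral palsy, epilepsy, hearing loss, and visual impairment", so deaths are foreseeable, but no rate is given. Section 2.10 justifies the size only by stating that "a sample size of 25 was considered adequate to reach saturation and establish feasibility", and makes sizing of the larger trial conditional on the feasibility criteria being met. Table 1 also lists, among the secondary aims, "Correlation of brain metrics with neurological outcome", to be analysed by regression with ASQ scores at 6 and 12 months. Death is given no place in that outcome.

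**The concern.** A retention criterion should show whether the follow-up procedures work. With all consented infants in the denominator, criterion (iii) also measures mortality. Contact procedures could work well and the criterion still be missed because several infants died, and the single percentage would not show which had happened. This matters because the criterion feeds the decision on whether the larger study is feasible.

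A related point concerns the ASQ regression. Infants who die have no questionnaire score, so the regression describes survivors only. In a study about prognosis that restriction should be stated, because the estimates are meant to inform the size of the definitive study.

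**Working it through.** The plan gives no calculation behind the criterion, so there is no stated figure to reproduce.

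**Inputs**
- Number consented: n = 25 (section 2.10).
- Criterion (iii): 80% of consented infants (section 2.8, Table 1). 0.80 × 25 = 20, so at least 20 successes and at most 5 failures.
- Criterion (ii): 90% of consented infants. 0.90 × 25 = 22.5, so at least 23 successes and at most 2 failures.
- Death rate d before 12 months: not given; assumed 0 to 20%.
- Questionnaire completion among survivors c: not given; assumed 90%, varied below to 95% and 85%.

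**What deaths do to the margin in (iii).** With k deaths, the completion needed among survivors is 20/(25 − k): 20/24 = 83% for one death, 20/22 = 91% for three, 20/20 = 100% for five.

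**Chance of meeting (iii), all-consented denominator.** X ~ Binomial(25, c(1 − d)); the chance is P(X ≥ 20).

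**Chance of meeting (iii), survivor denominator.** The number of deaths is K ~ Binomial(25, d). Given K = k, at least 80% of m = 25 − k survivors must complete, rounded up to a whole infant. The chance is the sum over k of P(K = k) × P(Binomial(m, c) ≥ ⌈0.8m⌉).

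Results with c = 0.90:

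| Deaths d | c(1 − d) | All consented | Survivors |
|---|---|---|---|
| 0% | 0.900 | 0.97 | 0.97 |
| 5% | 0.855 | 0.86 | 0.94 |
| 10% | 0.810 | 0.67 | 0.93 |
| 15% | 0.765 | 0.45 | 0.93 |
| 20% | 0.720 | 0.26 | 0.93 |

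Completion among survivors is 90% in every row, so the fall in the third column comes from mortality alone. The survivor column dips slightly because 80% of a smaller number rounds up; for example, 24 survivors still need 20.

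**Sensitivity to c** (all consented versus survivors, at 5, 10 and 15% deaths):
- c = 0.95: 0.97, 0.86, 0.65 versus 1.00, 1.00, 0.99.
- c = 0.85: 0.65, 0.45, 0.27 versus 0.76, 0.76, 0.77.

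**Criterion (ii).** Only two failures are allowed. Three infants without a recording in the window, for any reason, cap the result at 22/25 = 88%, which misses the criterion even if every other infant is recorded. If 5, 10 or 15% of infants cannot be recorded in the window (assumed) and all others are, P(X ≥ 23) is 0.87, 0.54 or 0.25. The text does not allow the share of such infants to be estimated.

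**The case against.** An all-consented denominator is a legitimate, conservative choice. It gives the share of consented infants who yield usable data, and the main study needs that figure for planning. Section 2.8 also promises a record of follow-up procedures and dropout rates, and the tabulation of reasons for loss is often left to a fuller document. The size of the effect rests on assumed rates: at 5% deaths the gap is moderate, 0.86 against 0.94. The article sets success criteria but does not say what follows a narrow miss.

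Most of this stands, and it is why the all-consented figure should be kept. It does not remove the point, because the article itself fixes a denominator that does not fit the purpose it states for the metric.

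A reader might infer more than the documents support:
- **Infants on respiratory support cannot be measured and so fail (ii).** Section 2.7.2 does say "All infants will be breathing spontaneously in room air", and section 2.11 collects ventilator days, home oxygen and tracheostomy. But the exclusion criteria are in Figure 1, which is not shown, and an infant ventilated early and then weaned fits both sections.
- **Failing (ii) means leaving the DOT analysis.** Table 2 places the DOT measurement under 4–15 days, so an infant recorded after day 7 misses (ii) but may still be analysed.
- **Infants on support also fail (iii).** A parent can complete the questionnaire for a surviving infant on support.
- **The severe group would be nearly empty, or event-rate inputs would be biased.** No severity mix or mortality by stage is given, and no event rate is planned. That losses fall more heavily on severe encephalopathy is plausible, but the text does not establish it.

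**Conclusion.** The point holds for criterion (iii) and the 12-month follow-up rate: both count a death after consent as a failure of retention, in a condition for which the article itself names death as an important outcome. With 25 infants and an assumed 90% completion among survivors, deaths of 5, 10 and 15% lower the chance of meeting the criterion to 0.86, 0.67 and 0.45, against 0.94, 0.93 and 0.93 on survivors. The effect is moderate at low mortality and large from about 10%. Both rates are assumptions, and deaths and completion are treated as independent between infants. This is a mismatch between the metric and its purpose, not an arithmetic error.

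For criterion (ii) the weakness is narrower: with only two failures allowed, the percentage alone will not show whether a miss reflects clinical course or study procedures. No claim is made about how many infants would be affected by the room-air condition.

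**What to change.** 1. Judge criterion (iii) on consented infants alive at the assessment date, at 6 and at 12 months. Report the all-consented percentage and the number of deaths beside it, and do the same for the 12-month follow-up rate.
2. Keep criterion (ii) on all consented infants, and tabulate the reasons for no recording (death, recording conditions not met, withdrawal, logistics) by Sarnat stage.
3. State that the ASQ regression applies to survivors. A rank-based sensitivity analysis with death as the worst outcome is an option, not a necessity, at this sample size.
4. Reconcile the 7-day limit in criterion (ii) with the 4–15 day column for DOT in Table 2, since the two decide differently which recordings count.

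The cost is a few sentences and one small table; no study procedure changes. The drawback is a slightly more favourable retention figure, which showing both denominators offsets.

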### 2.7. Interventions

#### 2.7.1. Study Equipment

In this study, we will use a multichannel fNIRS system—the Brite MKII (Artinis Medical Systems, Einsteinweg, The Netherlands)—a wearable and flexible device designed to measure cerebral oxygenation. Each unit can record up to 27 channels, with sensors (comprising both transmitter and receiver elements) arranged on a recording cap. Two devices will be used concurrently to achieve comprehensive coverage of the neonatal scalp. By positioning channels across distinct brain regions, we can simultaneously monitor neural activity in these areas. Each transmitter optode incorporates light-emitting diodes (LEDs) that emit near-infrared light at wavelengths of 760 nm and 850 nm. These wavelengths are used to estimate changes in oxygenated and deoxygenated hemoglobin. The system operates in continuous-wave mode at a frame rate of 10 Hz. The imaging cap is engineered with preconfigured apertures for sensor placement, which connect to a compact unit weighing approximately 300 g. Data are acquired and stored on the device for subsequent analysis.

The equipment can be set up quickly, is robust against motion and environmental noise, has high resolution, and is silent, which makes it suitable for neonatal use. The device is comfortable due to its soft optodes and rubber optode holders, which provide optimized flexibility for testing within neonatal settings. The device uses non-ionizing radiation and is non-invasive. The optodes will be placed on the neonatal scalp for a maximum of 45 min. During this short application duration, the likelihood of skin irritation is minimal. The Brite MKII is not licensed in Canada but has been authorized by Health Canada as an investigational device only for this research study (Figure 2a,b).

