#### 2.7.3. Data Acquisition

Before initiating data acquisition, the fNIRS recording device will be prepared by establishing a high-fidelity wireless connection with OxySoft software (OxySoft 4) and ensuring the device is ready for measurement. The recording device and the computer will be placed on a hospital cart and brought into the NICU. The cart is positioned adjacent to the crib, and the fNIRS device will be set beside the patient (Figure 2b). Next, the NIRS cap will be placed on the patient’s head and adjusted so that the central optodes align with the nasion and all optodes are positioned perpendicularly to the scalp with adequate contact. Once the cap is secured, an automatic signal calibration will be performed. A brief video of the patient wearing the cap will be recorded to co-register the recording channels with brain regions.

OxySoft is proprietary software specifically designed for facilitating the collection, storage, visualization, and analysis of fNIRS data. It supports the parallel recording of multiple devices, enabling synchronized data acquisition from multiple fNIRS units. In this study, OxySoft version 4.0 will record, manage, export, and monitor data in real time during measurements. OxySoft provides data acquisition (DAQ) status and DAQ values during signal calibration and data collection, conveying information such as device status, recording time, total recording duration, and the amount of light detected in each fNIRS recording channel. Channels whose light levels exceed or fall below acceptable thresholds are highlighted in red. Such out-of-range values may arise from head movements that displace the cap, environmental noise, or the presence of hair between the optode and the skin. If this occurs during signal calibration, the cap will be readjusted to optimize optode–scalp contact and calibration will be repeated until the light levels fall within the acceptable range. The research team will continuously monitor the DAQ values throughout the study.

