**Figure 5 neurosci-06-00060-f005:**
[figure not shown]
Demonstration of the principle of DOT, which uses differing absorption of infrared light by deoxygenated and oxygenated hemoglobin to measure changes in cortical blood flow in accordance with the Beer–Lambert Law.

**Table 1 neurosci-06-00060-t001:** Summary of the study objectives, outcomes, and analysis plans.

Objectives	Outcomes	Criteria for Success	Method of Analysis
Primary Aims			
Assess the feasibility of recruitment and retention strategies and data collection methods in the NICU.	Recruitment and retention rates, missing data.	(i) 80% of the eligible patients consent to the testing; (ii) 90% of the consented participants get DOT measurements taken before 7 days of life; (iii) for 80% of the consented participants, parent-reported developmental assessment is available at 6 and 12 months; (iv) Time required for resting-state data acquisition per infant < 45 min.	Descriptive statistics (mean and SD) for continuous variables. Proportions for dichotomous variables.
To assess the fidelity and safety of DOT measurements in neonates.	Adverse reactions, adequate measurements, and time for data acquisition.	(i) Reporting any adverse skin reactions to sensors or excessive agitation in the neonate requiring early termination of the study. (ii) Data quality will be assessed by recording the degree of the signal-to-noise ratio.	Qualitative analysis.
To identify logistic challenges, unexpected adverse effects, or technical difficulties.	Adverse events or operational difficulties.	An adequate amount of time and number of personnel required for each stage of the study and staff workload. Lack of logistic challenges.	Qualitative reporting.
To gain stakeholder engagement, including from parents and NICU nurses.	Engagement level.	Positive perceptions about the study procedures from parents and nurses.	Qualitative survey analysis.

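### The only numeric criterion tied to DOT fidelity, acquisition under 45 min, cannot separate usable from unusable recordings, and no other numeric feasibility criterion does so

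*Protocol article*

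**What the plan says.** The Introduction names the fidelity and safety of DOT measurements as the second of two primary objectives. Section 2.8 makes the feasibility of the main study depend on success against predefined criteria.

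For Objective 2 (fidelity and safety), section 2.8 gives one criterion: "Time required for resting-state data acquisition per infant < 45 min". It follows three listed outcomes:

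- Adverse skin reactions, or agitation that forces early termination, are to be reported.
- Data quality is to be recorded as a signal-to-noise ratio, along with sensor contact and artifacts: "We will keep a record of the ability to properly place sensors with good contact and the ability to minimize motion artifacts".
- The third outcome is "Ability to complete adequate data acquisition within 45 min".

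The procedure sets its own time limits. Section 2.7.1 states "The optodes will be placed on the neonatal scalp for a maximum of 45 min". Section 2.7.2 states "The total duration of the resting-state data acquisition will range from 30 to 45 min, depending on the infant’s cooperativeness". Section 2.7.3 says that, once the cap is secured, "calibration will be repeated until the light levels fall within the acceptable range".

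Under Objective 1 the criteria are consent in 80% of eligible patients, a DOT measurement taken before 7 days of life in 90% of consented participants, and parent-reported assessments in 80%. Table 1 moves the 45-min rule to the recruitment and retention aim. Its fidelity-and-safety row gives as criteria for success the reporting of reactions and "Data quality will be assessed by recording the degree of the signal-to-noise ratio", to be analysed qualitatively.

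**The concern.** A criterion for fidelity should be harder to meet when recordings are poor. This one measures elapsed time, which the procedure already limits, and says nothing about what was recorded. It also states no share of infants that must meet it. The other DOT criterion counts a measurement as soon as it is taken.

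At stake is the decision on the larger study. If the stated rule is applied as written, the main study could be declared feasible while many channels or minutes are lost in preprocessing. The criterion also has an awkward edge: a recording that uses the full permitted time fails, although it may be the most complete one.

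**Working it through.** The plan gives no formula or calculated figure for this criterion, and section 2.10 justifies 25 infants on practical grounds, so there is nothing to reproduce. The check compares the time limits with the criterion and then looks for a quality condition elsewhere.

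**Step 1. Permitted durations against the criterion.** Planned acquisition is 30 to 45 min (section 2.7.2), with optode placement at most 45 min (section 2.7.1). The criterion is strictly below 45 min.

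- 30, 35, 40 and 44.9 min: permitted, pass.
- 45 min: permitted, fails.

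The single permitted value that fails is the upper limit itself. Data quality does not enter the comparison.

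**Step 2. Is quality required anywhere else?**

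- Consent, 80%: no recording involved.
- DOT before 7 days, 90%: counts measurements taken.
- Parent-reported assessments, 80%: no recording involved.
- Time below 45 min: elapsed time only.
- Table 1, fidelity row: reporting activities, no pass value.
- Table 1, logistics and stakeholder rows: qualitative, none requires usable data.
- Section 3, preprocessing step 2: excludes poor channels, but states no minimum to be retained.
- Section 4: refers to acceptable signal quality, but neither defines it nor links it to the feasibility decision.

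Of the four numeric criteria, none requires a usable recording. Taken literally, all four could be met at any usable share from 0/25 to 25/25.

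**Step 3. What a usable-recording rule would add.** For illustration, assume a rule of at least 80% adequate recordings, with 25 independent infants who share one true adequate rate p. The 80% is an assumption and is not in the plan. The rule needs 0.80 × 25 = 20 infants. P(pass) = P(X ≥ 20), with X ~ Binomial(25, p):

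- p = 0.50: 0.002
- p = 0.60: 0.029
- p = 0.70: 0.19
- p = 0.80: 0.62
- p = 0.90: 0.97

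Such a rule responds strongly to data quality. An observed 20/25 has an exact (Clopper–Pearson) 95% CI of 59.3% to 93.2%.

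**Step 4. One proportion, not two.** If adequate recordings became the numerator of the 90% criterion, 0.90 × 25 = 22.5, so 23 infants would be needed (23/25: exact 95% CI 74.0% to 99.0%). Beside an 80% rule for Objective 2, results of 20 to 22 out of 25 would pass one rule and fail the other.

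**Step 5. Cap-on time.** Within the 45-min placement limit, a 30-min acquisition leaves 45 − 30 = 15 min for calibration with the cap on. A 45-min acquisition leaves 45 − 45 = 0 min, yet calibration may be repeated with no stated limit. The passages conflict only towards the upper end of the planned range.

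**The case against.** The strongest reply is the third outcome, which stands directly before the criterion: "Ability to complete adequate data acquisition within 45 min". Read with it, the time required is the time to complete an adequate acquisition. A recording abandoned after a few minutes would then not pass. It would also fall short of the 30-min lower limit and be captured as an early termination. This is a fair reading and it stands as far as it goes. It does not rescue the criterion, because adequacy is defined nowhere and the word is absent from the criterion in both section 2.8 and Table 1.

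Second, other text works against wholly unusable data. Calibration is repeated and light levels are monitored (section 2.7.3), section 4 lists contingencies for poor signal, and section 2.10 bases the larger study's sample size on the data analysis. These make the extreme case unlikely and mean that quality would be seen. None of them is part of the stated feasibility rule.

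Third, this is a condensed article, and numeric signal cut-offs often sit in a full protocol or analysis plan. That is right for the cut-offs. It does not answer the point that the criteria the article presents as predefined do not depend on quality.

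A reader might infer that the time criterion is certain, or nearly certain, to be met. The documents do not support that. They give no distribution of durations and no required share of infants; if every infant must comply, one full 45-min recording would fail the criterion. A reader might also infer that fidelity is the pilot's main purpose. The Abstract puts recruitment and retention first, and fidelity is one of two primary objectives.

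**Conclusion.** The point holds in a limited form and should be fixed. The stated numeric criteria for feasibility do not depend on whether DOT recordings are usable: none of the four contains a quality condition, and the one attached to fidelity can fail, among permitted durations, only at exactly 45 min. In Table 1 the fidelity-and-safety row has no numeric criterion at all.

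This rests on reading the criteria as worded. Under the more generous reading through the third outcome, what is missing is narrower but the same in kind: a definition of adequate and a required proportion of infants. It would go too far to say that a decision to proceed would carry no information about measurability, because signal-to-noise ratio, contact and artifacts are to be recorded and described. No probability of passing the current time criterion can be calculated from the documents.

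**What to change.** - **Objective 2 criterion.** Restate it as the proportion of infants with an adequate recording. Define adequate in advance by the plan's own 30-min lower limit and a sponsor-set minimum share of the 54 channels (27 per side × 2, section 2.7.2) retained after preprocessing step 2. State the 54 explicitly, since section 4 mentions only 27 channels. Count early terminations as failures.
- **DOT criterion under Objective 1.** Make adequate recordings its numerator, and set one required proportion and denominator consistent with Objective 2.
- **Reporting.** Give n/N with an exact 95% CI.
- **Time rule.** If kept, word it as 45 min or less, so that a full-length recording does not count as a failure.
- **Table 1.** Place the new criterion in the fidelity-and-safety row and align it with section 2.8.
- **Time limits.** Reconcile the maximum optode placement in section 2.7.1 with the acquisition range in section 2.7.2 and the repeated calibration in section 2.7.3. Report total cap-on time separately from acquisition time.

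The cost is protocol wording. Recording duration is already shown by the acquisition software (section 2.7.3), and channel exclusion is already a preprocessing step (section 3). The sponsor has to choose the channel share and the required proportion before seeing data, and the criterion can then fail.

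### The acquisition-time success criterion sets its pass mark at the planned 45-min ceiling and drops the adequacy condition, so it barely discriminates as worded

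*Protocol article*

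**What the plan says.** Four statements in the Protocol article bear on the 45 min.

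- **Criterion** (section 2.8, Objective 2; repeated in Table 1, first row, item iv): "Time required for resting-state data acquisition per infant < 45 min".
- **Outcome that it serves** (Objective 2(iii)): "Ability to complete adequate data acquisition within 45 min".
- **Planned length** (section 2.7.2): "The total duration of the resting-state data acquisition will range from 30 to 45 min", varying with how settled the infant is. The Abstract gives the same period.
- **Contact limit** (section 2.7.1): "The optodes will be placed on the neonatal scalp for a maximum of 45 min".

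Section 2.7.3 describes the session. It opens with "Before initiating data acquisition, the fNIRS recording device will be prepared". The cap is then fitted and adjusted on the head. After that, "Once the cap is secured, an automatic signal calibration will be performed", and this is repeated if light levels are out of range. Also, "A brief video of the patient wearing the cap will be recorded". The software is said to report "DAQ values during signal calibration and data collection". No duration is given for any of the set-up steps.

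**The concern.** A feasibility criterion should be one that a failing pilot could fail. Here the threshold equals the top of the range that the plan already prescribes for the same quantity, and nothing in the criterion asks for a minimum length or for usable data.

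It is one of four success criteria in the first row of Table 1, and the only one with a number attached to how the bedside recording goes. Criterion (ii) asks only that a measurement is taken before 7 days of life. The fidelity row asks that signal-to-noise be recorded and adverse reactions reported, without thresholds. Objective 3 looks at time per stage, again without a threshold. The larger study needs to know whether a usable recording can be obtained within the permitted contact time. As worded, meeting this criterion says little about that.

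A second, conditional issue follows from using the same 45 min for acquisition and for contact. Any on-head set-up outside the acquisition clock has no room at the top of the planned range.

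**Working it through.** The threshold is stated, not derived, so there is no plan figure to reproduce. The check compares the limits with one another.

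**Inputs**
- A = acquisition time, planned 30 ≤ A ≤ 45 min (section 2.7.2, Abstract).
- Criterion: A < 45 (Objective 2, Table 1).
- Contact limit C ≤ 45 min (section 2.7.1).
- s = on-head set-up time (fitting, calibration, video). It is **not stated**. The article calls set-up quick, calibration automatic and the video brief, so s = 1, 2, 3 and 5 min are assumed for illustration.

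**Step 1: what can fail A < 45?** Within the planned range, every value from 30 up to but not including 45 passes; only A = 45 fails. Yet A = 45 is allowed by section 2.7.2 and satisfies Objective 2(iii), which accepts acquisition within 45 min. Below the range, a recording stopped at, say, 10 min for agitation gives 10 < 45 and passes on the literal wording.

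**Step 2: is set-up inside or outside A?** Two features suggest outside: preparation is placed before acquisition begins, and calibration is named separately from data collection. One points the other way: all these steps stand under the heading Data Acquisition. The text does not settle it.

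**Step 3: contact time if set-up is outside A.** C = s + A, so C ≤ 45 requires A ≤ 45 − s. The part of the 15-min-wide planned range (45 − 30) above that limit is s/15.

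| Assumed s (min) | Longest A within the contact limit (45 − s) | Contact at A = 45 (45 + s) | Share of planned range over the limit (s/15) |
|---|---|---|---|
| 1 | 44 | 46 | 6.7% |
| 2 | 43 | 47 | 13.3% |
| 3 | 42 | 48 | 20.0% |
| 5 | 40 | 50 | 33.3% |

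The last column is a share of the range's width, not of infants. Reading it as infants would need an assumed distribution of A.

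**Step 4: the two limits together.** If staff keep C ≤ 45 and s > 0, then A ≤ 45 − s < 45. On this reading even the one failing value in Step 1 cannot occur, and no recording can fail on time alone.

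**Step 5: if set-up is inside A.** The contact conflict of Step 3 disappears. Step 1 is unchanged: the pass mark is still the planned ceiling.

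**Step 6: room under a cap-on clock.** With a 30-min minimum inside a 45-min contact window, 45 − 30 = 15 min is left for on-head set-up.

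**The case against.** The best defence is that time required is not time spent. The criterion directly follows the outcome about adequate acquisition within 45 min; read together, an infant who has not yielded adequate data by 45 min fails, and an early-stopped recording would not pass. This has force. It means a reader should not infer that the criterion is empty or can never be failed: a sympathetic reading gives it content. But the criterion does not carry the adequacy condition, either in Objective 2 or in Table 1, so someone applying it as written would not test for it.

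A reader might also infer that Table 1 misplaces the criterion by listing it with recruitment and retention. The documents do not support that: the row also covers data collection methods, and the fidelity row lists adequacy and time side by side.

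Third, the contact conflict rests on a contestable reading. The opening phrase of section 2.7.3 strictly governs preparation of the device, which happens off the head, and the phrase about calibration and data collection describes what the software shows. Staff can also respect both limits by stopping early. This stands, so the conflict can only be stated conditionally.

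Finally, much is recorded anyway: signal quality and sensor contact per infant, time per stage, and parent and nurse views on duration. The larger study would still receive that information. None of it, however, sets a threshold for success. Nor is this detail left to a fuller document: the article itself fixes the criterion as predefined.

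**Conclusion.** The criterion is badly fixed, and the consequence is minor. On its literal wording nearly every recording passes, including one stopped early, and the only planned length that fails is the full 45 min that the plan permits. This follows from the stated figures alone.

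The contact-time overrun is conditional on set-up lying outside the acquisition clock. In that case the overrun equals the set-up time, and the 1 to 5 min shown rests wholly on assumed values. A reader might conclude that the 45-min contact maximum simply cannot be kept. The documents do not support that: there is no conflict for acquisitions of 45 − s or shorter, and none at all if set-up is counted within acquisition.

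Nor is there a material safety finding. The device is soft and non-invasive, and skin reactions and agitation are reported regardless. The sample size of 25 rests on practical grounds and is unaffected, as are error rates.

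**What to change.** Restate the criterion in Objective 2 and in Table 1 item (iv) as: at least 30 min of resting-state acquisition obtained within 45 min of cap-on, per infant. Both figures are the plan's own. The 30 min is the lower end of the planned range, not a declared usability minimum, so the investigators may substitute another value if they have grounds for one. Log cap-on and cap-off times, and report acquisition time separately. The criterion can stay in its present Table 1 row.

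The cost is a wording change in two places and two time stamps per infant (2 × 25 = 50), with no extra staff. The downside is that some recordings will be shorter, because set-up now uses part of the 45 min, and the feasibility result may look less favourable.
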